#### 3.2.2. Public Attitudes, Stigma, and Taboo

The online survey among the general public partly replicates the baseline questionnaire for the general public of the Optimising Suicide Prevention Programmes and Their Implementation in Europe (OSPI-Europe) study [19], with Dutch translations of the Depression Stigma Scale [17] and the Attitude Towards Seeking Professional Psychological Help short form [18] (Table 1). We added questions about (talking about) suicidal behaviour, experience, taboo, and the Suicidal Ideation Attribution Scale (SIDAS) [15].

Changes in help-seeking behaviour, stigma, talking about suicide, and taboo around suicide will be analysed using GLM repeated measures. We will compare the results over time, as well as time × effect interactions to reveal if a SUPRANET community is differently (more) effective than the nationally-observed changes.

#### 3.2.3. Help-Seeking Behaviour to the Dutch Suicide Prevention Crisis Service 113

In addition to measuring an intervention effect within the general public with self-reporting, an intervention effect will also be measured by analysing the volume of crisis calls to the helpline of 113 Suicide Prevention. A significant increase in monthly calls during and just after the three waves of the public awareness campaign is hypothesized compared with the same months in the previous year [20]. Furthermore, due to the multicomponent approach, we expect bigger increases in crisis calls in the SUPRANET regions compared with the control region (i.e., national data outside the SUPRANET communities) [20]. This is feasible since the place of residence of each caller is monitored.

### 3.3. Evaluation of the Feasibility and Process of SUPRANET

In addition to evaluating the impact of the SUPRANET intervention in the ways described above, we will conduct an evaluation with the aim to: (1) generate an overview of the actors, situations, sites, and contexts involved in the SUPRANET implementation process and the main implementation activities undertaken within the regions; (2) create an insight into the degree to which suicide prevention is actually embedded into routines, or “normalized” in daily practice and routines, identify the barriers and facilitators to and in implementing the four-level intervention, and illuminate recommendations for broader dissemination of the EAAD approach in The Netherlands; and (3) study the impact of the SUPRANET interventions on professional performance.

#### 3.3.1. Overview of the Reach of the SUPRANET Components, Actions, and Interventions in Each Community

To generate an overview of the reach of SUPRANET, and to reveal intermediate effects on the outcomes, all specific actions and interventions related to the four components of the SUPRANET approach in each of the intervention regions are monitored. For the public awareness campaign, the amount of posters, flyers, etc., for each region is registered, as well as the location. Furthermore, questions on awareness and recognition (seen, read, or heard) the media campaign are asked in the general public in the online survey. Another example of monitoring the reach of each SUPRANET component in each region is the number of community facilitators that are trained as gatekeepers.

Every six months (November 2016, May 2017, November 2017, May 2018, and November 2018) we will ask the regional implementer of each SUPRANET community to fill in an online survey, with questions about the actors, sites, and contexts involved in the SUPRANET implementation process and the main implementation activities undertaken within the regions according to the Re-Aim Model (Reach, Effectiveness, Adoption, Implementation, Maintenance). Since it is possible for each region to fine-tune each of the four SUPRANET components and enrich them with local strategies, thus developing a context specific suicide prevention plan, the survey also monitors additional local strategies and interventions. Additional local interventions will be monitored by 113 and evaluated by the epidemiologists working at the local Public Health authorities.

#### 3.3.2. Identifying the Barriers and Facilitators to, and in Implementing, the Four-Level Intervention

During the process evaluation the Normalization Process Theory (NPT [21]) will guide our decisions about the predominantly qualitative data collection and analysis. NPT is designed to evaluate the effect of multi-component interventions in a dynamic environment. NPT encourages researchers to follow implementation processes, by focusing on a range of people, situations, times, and places that are involved in all aspects of enacting that process. NPT helps to make sense of collective, distributed, patterns of work.

NPT helps to classify complex implementation work that people do around four conceptual constructs: coherence, cognitive participation, collective action, and reflexive monitoring. Coherence refers to how people individually and collectively make sense of the situation when they are faced with the problem of operationalizing complex interventions, in our case suicide prevention activities. It implies that the actors have a shared understanding of what constitutes the suicide prevention work. Cognitive participation is the relational work that people do to build and sustain a community of practice around the suicide prevention work. Collective action is about how suicide prevention is organized and what factors constrain and structure the activities. The fourth mechanism of reflexive monitoring is about the appraisal of the suicide prevention work and the modifications the actors may propose to make the suicide prevention activities workable in practice.

We will purposefully select settings and individuals within the SUPRANET communities to participate in the process evaluation. This means that we will select respondents beyond the “usual” respondents, like the health professional or patient. We will focus on others who are vital within suicide prevention, those that are less visible and often omitted from implementation studies. For example, receptionists in GP practices, debt counsellors, clergymen, and sports coaches. They have to accommodate and realise aspects of adequate suicide prevention. NPT also recommends selecting a large range of sites and contexts, beyond the usual situations, times, and contexts of health care research. We will follow the regional networks for 18 months during their implementation journey in different situations and places: the local project management table, local health authorities or mayor’s offices, GP practices, social community teams, the benefits payment offices, and so forth. We will also pay attention to the diffuse situations where suicide prevention work is discussed, complained about, or praised.

Methods of data collection for this part of the evaluation are as follows:(1)Every three months semi-structured interviews will be conducted with the seven project managers in charge of the overall coordination within each SUPRANET community, and (at least) three other relevant participating stakeholders (to be selected purposefully at every interview period) per community. The interviews will focus on the implementation processes and activities and the facilitators and barriers of and to the implementation process per program component. Over the course of the intervention, we will interview and survey SUPRANET participants from different backgrounds and settings: those involved in the local implementation/project teams and those involved in the organisations that will actually implement the suicide prevention interventions. The interviews will be analysed using the NPT framework.(2)During the period of the SUPRANET community program (2017–2018) relevant documents supporting the implementation process of the regions will be analysed (such as work plans, policy documents).

Since, the interviews will be conducted every three months with 3–5 persons per region, surveys will be held every six months with all seven local project leaders, and every six months the project environment will be screened for relevant documents regarding the implementation process; after 18 months this will lead to a total of approximately 125 to 200 interviews, 21 surveys, and a number of documents produced by the regions.

We will use all data sources to perform the analysis and answer our research questions (triangulation). The surveys will be analysed by listing actors and settings, barriers and facilitators, and by thematic analysis of the qualitative information. The interviews will be coded using thematic analysis, and grouped under the various NPT constructs and components. Thematic analysis consists of a process of coding in six phases to create established, meaningful patterns. These phases are: familiarization with data, generating initial codes, searching for themes among codes, reviewing themes, defining and naming themes, and producing a scientific publication and recommendations for broader dissemination of the program in The Netherlands [22].

#### 3.3.3. Impact of the Intervention on Professional Performance: Gatekeepers Attitude, Knowledge, and Skills

The gatekeeper intervention will be evaluated within the SUPRANET communities with measurements before and after the gatekeeper training sessions. We will use a baseline questionnaire prior to the start of the training and a follow-up questionnaire six weeks after. This is already a standard procedure for the gatekeeper training sessions given by 113 Suicide Prevention.

Gatekeepers’ identification of people with suicidal thoughts, referrals to professional care, knowledge of suicidal behaviour, and confidence in their abilities to talk about suicide will be evaluated with an instrument based on other gatekeeper training surveys [23], added by questions assessing confidence on talking about suicide [24]. We hypothesize that the training has a significant impact on gatekeepers’ referral behaviour, knowledge of suicide prevention activities, and confidence in their abilities to ask about suicide [23,24]. Furthermore, we expect that within the SUPRANET communities, relatively higher numbers of gatekeepers will be trained when compared to national numbers.

#### 3.3.4. Impact of the Intervention on Professional Performance: Identification of Depression and Suicide (Attempt) within Primary Care

Using the NIVEL primary care database (NIVEL-PCD) we can extract incidence and prevalence rates of depression and suicide (attempt) for individual general practice. NIVEL-PCD is one of the largest primary care databases in Europe, covering more than 500 GPs with a total practice population of 1.6 million individuals. NIVEL-PCD collects routine electronic health record data, including health problems, consultations, prescriptions, and referrals. Health problems are ICPC coded (international classification of primary care) [25]. The database is representative of the Dutch population. If practices are participating in the intervention, but not yet connected to the NIVEL-PCD, we will include the practices in the NIVEL PCD for the time of the study. Within participating GP practices in all seven regions we will collect all registrations of P76 (depression), P03 (depressed feeling) and P77 (suicide (attempt) and compare the rates 12 months before the start of the project (January–December 2016) to those 12 months after the end of the two year program (January–December 2019). An increase in incidence is hypothesized, due to an increase in recognition of depression and suicidal behaviour within primary care after the suicide prevention training offered to GPs and mental health nurses in the SUPRANET communities. Within the GPs, for the year 2015, an incidence of 11.4 per 1000 patients with P76 (depression) was found, and an incidence of 9.6 for P03 (depressed feeling) For a standard practice with about 2500 patients, we expect around 30 new cases of P76 per year and 25 new cases of P03 per practice. Within one region with five GPs, we expect 275 new registrations of depression and depressive thoughts. Within the seven regions we expect around 1900 new cases of depression. Within the NIVEL registration, we will use a matched control group of around 30–40 practices. Given an alpha of 0.05 and a power of 0.8, this will allow us to detect a small effect size of 0.10.

Analysis will be carried out using multilevel regression techniques, with the incidence of depression and suicidal thoughts as the dependent variable and the condition (intervention or control) as the independent variable. Covariates will be the characteristics of the practices (urban/rural, distribution of age, solo practice, or group practice) and the incidence of depression and suicidal thoughts before the intervention. The different levels are the region, the general practice and the patient.

Furthermore, to measure change in guideline adherence, we will look at the key recommendation of the Dutch guidelines, i.e., the exploration of suicidal ideation and concrete suicide plans by GPs and/or primary care nurses [26,27] within the group of depressed patients. We will measure this by making use of a procedure similar to the one used within the sentinel practices of NIVEL Primary Care Database. Monthly, all new contacts for P76 (depressive disorder) within the electronic medical record of the intervention practices will be extracted by a research or doctor’s assistant. The GP or the mental health nurse will be asked to retrospectively answer an additional short questionnaire for each patient about whether or not suicidal thoughts have been explored, what was the level of intensity of the thoughts and concreteness of suicidal plans, and what actions/interventions were proposed/agreed upon. The questionnaire has been developed by experts and based on the recommendations of the Dutch suicide prevention guideline [26], and are added in supplement 1. These are basic elements of the gatekeeper training offered to GPs and mental health nurses in the SUPRANET communities. We will compare the answers of the intervention practices with data collected within a non-randomized group of 40 sentinel practices, a nationally representative subgroup of practices participating in NIVEL Primary Care database with in total 120,000 registered patients (0.7% of the Dutch population). Via these sentinel practices, NIVEL will collect additional data on suicide and suicide attempts over the last 30 years. In these practices an electronic tool incorporated in the EMD of the GP, the P-module, asks for additional information from the GP triggered by the use of an ICPC code, in order to discriminate between cases and non-cases. If a case is defined, the application generates an additional electronic questionnaire about the characteristics of the patient and the content of the GP encounter. In the past 30 years such an additional questionnaire has been used in suicidal patients after fatal and non-fatal suicide attempts indicated by ICPC-code P77 used by the GPs [28]. For the present study a new category has been defined with an extension of the P-module and an extra electronic questionnaire related to TCPC code P76.

We hypothesize that, within the intervention practices, suicide ideation will be more often explored within depressed patients after the suicide prevention training offered to primary care staff (2017–2018) as part of the intervention, when compared to the period before the training (2016) and when compared to those sentinel practices who are not part of the intervention group and did not have the training.

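### Intervention practices outside the NIVEL database are connected because they take part, while all controls are registry practices, so any change in recording on joining would fall in one arm only and in the hypothesised direction

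*Protocol article*

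**What the plan says.** All of this is in section 3.3.4 of the protocol article unless noted.

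- **Outcome.** In the participating practices of all seven regions, "we will collect all registrations of P76 (depression), P03 (depressed feeling) and P77" (suicide or attempt). Rates in calendar 2016 are compared with rates in calendar 2019.
- **Hypothesis.** "An increase in incidence is hypothesized, due to an increase in recognition of depression and suicidal behaviour within primary care". The rise is put down to the training offered to GPs and mental health nurses.
- **Intervention practices.** Section 2.2.4 aims for at least five per region. On those outside the registry: "If practices are participating in the intervention, but not yet connected to the NIVEL-PCD, we will include the practices in the NIVEL PCD". The connection is for the study period.
- **Controls.** "Within the NIVEL registration, we will use a matched control group of around 30–40 practices".
- **Model.** Multilevel regression on condition. The covariates are urban or rural setting, age distribution, solo or group practice, and "the incidence of depression and suicidal thoughts before the intervention". No term concerns registry membership.
- **Further activity in intervention practices.** New P76 contacts are extracted monthly, and the GP or nurse completes a questionnaire for each patient.

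**The concern.** The outcome is what clinicians code, not what patients have. A practice that starts supplying coded records to a research registry may code more completely or register episodes differently. The article does not say that this happens, but the design lets it happen in one arm only. Controls are registry practices, whereas some intervention practices may become members because of the study.

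The direction matters. The plan expects recorded incidence to rise and will read the rise as better recognition. More complete coding after joining would give the same rise without any effect of training. The discussion presents the primary care component as a chance to assess the programme's effectiveness in that setting, so the two explanations need to be kept apart.

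**Working it through.** **1. The plan's own case count.**
- 2015 rates of 11.4 (P76) and 9.6 (P03) per 1,000, in a practice of 2,500 patients: 11.4 × 2.5 = 28.5 and 9.6 × 2.5 = 24.0. The article rounds these to 30 and 25, or 55 per practice.
- Per region: 55 × 5 = 275, as stated.
- Seven regions: 275 × 7 = 1,925, against about 1,900 stated. The chain reproduces.
- Controls at the same rate: 30 × 55 = 1,650 to 40 × 55 = 2,200 cases.

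**2. Timing of connection.** No connection date is given. The connection is announced in the future tense, in a text that already reports the February 2017 campaign wave as started (section 2.2.1) and the January 2017 survey as done (section 3.2.1). The natural reading is that practices still to be connected join after the baseline year, between the two measured years.

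**3. Why the covariates do not help.** Adjusting for 2016 incidence deals with a difference in level between practices. It does not remove a change in recording that begins after 2016 in one arm. Matching within the registry cannot balance new connection either, since no control is newly connected for the study.

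**4. Size, by assumption.** Let f be the share of intervention practices newly connected and g the relative rise in recording on joining. Take practices of equal size with equal recorded 2016 incidence, no true effect and no change in controls. The 2019/2016 ratio is 1 + g in new practices and 1 elsewhere, so

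spurious rate ratio = (1 − f) × 1 + f × (1 + g) = 1 + f × g.

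| f | g = 0.05 | g = 0.10 | g = 0.20 |
|---|---|---|---|
| 0 | 1.00 | 1.00 | 1.00 |
| 0.25 | 1.0125 | 1.025 | 1.05 |
| 0.50 | 1.025 | 1.05 | 1.10 |
| 1.00 | 1.05 | 1.10 | 1.20 |

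Neither f nor g is in the article.

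**5. Would ratios of this size matter?** The yardstick must be on the rate-ratio scale. With the case counts in step 1, two-sided alpha 0.05 and 80% power, the smallest detectable ratio for 2019 cases, with baseline treated as known, is exp[(1.960 + 0.842) × √(1/1,925 + 1/C)]. This is 1.10 for C = 1,650 and 1.09 for C = 2,200. For a comparison of changes the log ratio is multiplied by √2, giving about 1.14 and 1.13. With f = 0.5 and g = 0.20 (ratio 1.10) and no true effect, a comparison of changes would be significant with probability 0.53 to 0.59. With f = 0.5 and g = 0.10 (ratio 1.05) it is 0.18 to 0.20. These are Poisson approximations that ignore clustering. A correct multilevel model would lower the probabilities but leave the bias in place.

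**6. Would a membership term in the model solve it?** No. New connection is nested in the intervention arm, so with that term the condition effect rests on the previously connected practices alone. If there were only 3 of them (165 cases) against 35 controls (1,925 cases), the standard error of the log ratio is √(1/165 + 1/1,925) = 0.081. The detectable ratio is then exp(2.802 × 0.081) ≈ 1.25 for 2019 alone, or about 1.38 for a comparison of changes.

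**The case against.** The strongest reply is that the mechanism is assumed. The registry takes routine electronic records, and the article mentions no feedback, incentive or new coding rule on joining. No connection date is given, and regions were being selected from January to August 2016, so some practices might have joined that year. Collecting all 2016 registrations from a practice connected later already implies retrospective extraction from its own records. Episode and completeness rules are detail that an article may leave to fuller documents.

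Much of this stands, and it limits the point to a possibility of unknown size. It does not remove the asymmetry. The article itself fixes the rule for adding practices, the source of controls, the comparison years and the covariates. Retrospective extraction does not undo a later change in coding habits.

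A reader might infer three stronger things that the documents do not support.

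- **That nearly all practices would be new.** The article's figures imply registry coverage of about 9% (120,000 / 0.007 = 17.1 million; 1.6 / 17.1 = 9.3%), or about 3 of 35 practices already connected. That holds only if recruitment ignores membership, which is nowhere stated.
- **That the artefact equals the plan's target effect of 0.10.** That figure is called a small effect size and behaves roughly like a standardised difference: with cases as units, the detectable difference is 0.094 to 0.087. It is not a rate ratio and should not be set beside 1.10.
- **That a positive result could not be credited to the programme at all.** A bias that may be zero does not justify this.

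**Conclusion.** The concern holds as a design weakness of minor to moderate severity. The plan allows new registry connection in the intervention arm only, apparently after the baseline year. Any gain in recording would favour the hypothesis, and the stated covariates do not deal with it. The size cannot be determined from the article. It is zero if every participating practice is already a member or if coding does not change on joining. The illustrative spurious ratios of 1.05 and 1.10 (half new, coding gain of 10% or 20%) rest wholly on assumed inputs. The outcome belongs to Part 2 of the evaluation (Table 1), on professional performance, and is not one of the primary impact outcomes.

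**What to change.** - Extract 2016 and 2019 from each practice's own records with the same episode-construction rule.
- Include intervention and control practices in the incidence comparison only if they meet the same ICPC coding-completeness criterion in both years.
- Report how many intervention practices were newly connected, and when.
- Pre-state a sensitivity analysis giving the 2016 to 2019 change separately for previously and newly connected intervention practices, each against controls. If the rise appears only in newly connected practices, state that a change in recording cannot be excluded.
- Do not put a membership indicator in the main model, and do not make attribution depend on the previously connected subset, for the reason shown in the last step of the working.

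**Cost.** One retrospective extraction per new practice, one completeness rule and one extra table. Some practices may be excluded, and the previously connected subset may be imprecise. The check also leaves one source untouched: the monthly P76 extraction and questionnaire may influence coding in intervention practices whether or not they were already connected. The report should say so.
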